## 3.2 Primary and secondary endpoints (outcomes, outcome measures, Zielgrössen)

Endpoints are understood as significant changes in outcome measures (see 5.2 for Feature Description for further details)

(Ep) Primary endpoint: significant difference between mean MWT- and DS-MWT-latencies.

Additional, secondary, exploratory endpoints are

(Es-1) significant differences in driving parameters

(Es-2) significant differences in ET- and EEG-features

(Es-3) significant differences in @home-PSG-recordings and test sequence

(Es-4) significant correlation to biomarkers for sleepiness in saliva and/or exhaled breath

See 5.1.2 for statistical analysis plan

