## 3.3 Study design

This study is a monocentric, controlled, within-subjects, randomized, cross-over clinical trial on a cohort of OSAS patients. Two equivalent arms explore the influence of the test sequence per starting condition. Neither participants nor observers can be fully blinded.

Allocation to the starting condition (W or C) and one of two study arms (DM or MD) determining measurement sequence is required and will be randomized (lottery).

*A priori,* we do not allocate or stratify by study population characteristics, i.e., according to sex, age, medication, dosage, duration of treatment etc. We will, however, evaluate *post hoc*, whether outcomes are influenced by these factors.

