| Sampling 4/4 (blood, saliva, exhaled breath, dried blood spots) | 15 |  |  |  |  | +**^*^** |  |
| Checking PSG | 15 |  |  |  | +**^*^** | +**^*^** |  |
| Discussion, Outlook and Feedback (opt.) | 30 |  |  |  |  |  | +**^*^** |

As all data are recorded automatically (Silab, SAFE, EEG, ET) and/or without interference from the investigator (questionnaires), we do not expect observer or sequence biases here. Any adherence/reporting bias (e.g. participants incorrectly report their medication status or by-consumption) is controlled for by blood sampling. Attrition and stopping (partial reference) biases are minimized by the compensation scheme.

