## 5.2 Feature description

*Test-Latency:*

Mean MWT- or DS-MWT-latencies are determined by averaging latencies from four max. 40 min test- sessions determined by AASM-criteria (REF,) and previously reported additional/complementary parameters (e.g., sleep accidents with closed eyes, (1)) for the two tests, respectively.

*Driving Parameters*

We will collect multiple driving parameters, such as the standard deviation of lane position, SDLP, the standard deviation of velocity, SDS, number of lane departures, and LD. Collected parameters will also be used as one criterion to determine the sleep-accident-derived latency for the DS-MWT. IDS

*ET Features*

A recent review showed that eye movement features and the sleep-wake predictor model could be used to predict sleepiness (6). For example, the blink rate increases with increased sleep pressure and can be used to assess drowsiness or sleepiness. Other valuable ET metrics (5) for our setting are the saccade latency, saccade peak velocity and smooth pursuit velocity gain, which could also reflect levels of sleep deprivation and extreme sleepiness.

*EEG Features*

EEG recordings are required to determine MWT-latencies, based on precise identification of sleep onset (SO). According to AASM classification, sleep onset is defined as the start of the first epoch scored as any stage other than stage W. In most individuals this will usually be the first epoch of stage N1, characterized by SEM (slow eye movements) and LAMF (low-amplitude, mixed-frequency) in EEG activity. Electrophysiological data collected during both classical MWT and DS-MWT will provide useful additional insights into the sleep-wake transition. For example, microsleep episodes (MSEs), i.e., brief periods of sleep intrusion during wakefulness, may occur even before sleep onset. We will analyze manually- and automatically-detected MSEs (17).

*PSG Features*

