# 8 Quality CONTROL AND Data protection

## 8.1 Quality measures

For quality assurance the sponsor, the Ethics Committee or an independent trial monitor may visit the research sites. Direct access to the source data and all study-related files is granted on such occasions. All involved parties keep the participant data strictly confidential.

All study team members are trained in accordance with their assigned roles. Staff is trained to ensure reproducible and high data and analysis quality. The coordinating center of the monocentric study is based at the Division of Traffic Medicine. There are no steering and no endpoint adjudication committees appointed in this exploratory study. The data management team is identical to the investigators and part of the Division of Traffic Medicine.

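### Automatic recording does not justify expecting no observer bias: the primary latency is scored afterwards, and the protocol describes no masked scoring

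*Protocol*

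**What the plan says.** Section 4.3 gives a reason and a conclusion. The reason is "As all data are recorded automatically (Silab, SAFE, EEG, ET) and/or without interference from the investigator (questionnaires"; the conclusion is "we do not expect observer or sequence biases here".

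Other parts of the protocol bear on this:

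- **Primary endpoint (Section 3.2):** "significant difference between mean MWT- and DS-MWT-latencies". Sections 3.1 and 5.1.2 say that the primary hypothesis rests on mean latencies alone.
- **How latency is obtained (Section 5.2):** AASM staging, under which "sleep onset is defined as the start of the first epoch scored as any stage other than stage W", together with "previously reported additional/complementary parameters (e.g., sleep accidents with closed eyes, (1)) for the two tests, respectively". For driving data, the section adds: "Collected parameters will also be used as one criterion to determine the sleep-accident-derived latency for the DS-MWT".
- **Blinding (Section 3.3):** "Neither participants nor observers can be fully blinded". The synopsis attributes this to the schedule, the intervention and the measurement sequence.
- **Oversight (Section 8.1):** no endpoint adjudication committee is appointed, and "The data management team is identical to the investigators and part of the Division of Traffic Medicine".
- **Sequence (Section 3.1, objective O_s-1):** the study will explore whether test order affects the latencies.

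**The concern.** The conclusion in Section 4.3 does not follow from its reason. Automatic capture protects the raw signal. The primary outcome is a reading of that signal, made at a later step that the sentence does not consider. Section 5.2 says that onset is usually the first N1 epoch, recognised by slow eye movements and a change in EEG activity. Placing that boundary requires judgement.

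If the reader knows that a record comes from the simulator, or that an accident occurred at a given minute, scored onset can move in one test and not in the other. Comparing each patient with himself or herself does not remove such a shift, because it depends on the condition and not on the person. It could work in either direction. A shift away from agreement can create a false difference. A shift towards agreement can hide a true one, and no difference is the stated primary hypothesis.

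The sentence also dismisses sequence bias, while O_s-1 treats an effect of sequence on latency as an open question.

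**Working it through.** The plan states no figure for this bias, so there is none to reproduce. The main check is textual.

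**1. Does the reason cover the primary outcome?** Section 4.3 lists simulator data, the fitness-to-drive application, EEG, eye tracking and questionnaires. All of these are capture. Under Section 5.2, latency is the start of a scored epoch, supplemented by accident criteria. The protocol does not say that latency is scored automatically. Manual and automatic detection are both mentioned, but only for microsleep episodes, which are exploratory. The reason therefore stops one step short of the outcome.

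**2. Is there a safeguard elsewhere in the protocol?** Section 3.3 concedes incomplete observer blinding. Section 8.1 has no adjudication and makes the investigators the data managers. No section names the scorer or describes masked or duplicate reading.

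**3. Which knowledge can bias which comparison?** Each patient takes both tests within each phase (visits 3 and 4, then 6 and 7). Starting condition and test order are randomised.

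| What the reader knows | D versus M (primary) | CPAP withdrawal versus continuation, or sequence |
|---|---|---|
| CPAP state | Falls on D and M alike, so cancels in the main effect unless it interacts with test type | Biased |
| Test order | Balanced by randomising DM and MD | Biased |
| Test type or simulator accident | Biased | Affected only through interaction |

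**4. How large might it be?** This is an illustration only. From Sections 5.1.1 and 5.1.2: N = 36, SD = 13.5 min, significance at p<0.05. Assumed here: a differential scoring shift b of 2 min; correlation rho of 0.3 to 0.7, because Section 5.1.1 names a correlation but gives no value; k = 1 or 2 D-M pairs per patient, treated as independent; and a true difference of zero.

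SE = 13.5 × √(2(1 − rho)) / √(36k)

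P(p<0.05) = 1 − Φ(1.96 − b/SE) + Φ(−1.96 − b/SE)

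Example with rho = 0.3 and k = 1: SE = 13.5 × √1.4 / 6 = 2.66 min and b/SE = 0.75. P = 1 − Φ(1.21) + Φ(−2.71) = 0.113 + 0.003 = 0.117 before rounding.

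| rho | k | SE (min) | P(p<0.05) with a 2-min shift |
|---|---|---|---|
| 0.3 | 1 | 2.66 | 11.7% |
| 0.3 | 2 | 1.88 | 18.6% |
| 0.5 | 1 | 2.25 | 14.4% |
| 0.5 | 2 | 1.59 | 24.2% |
| 0.7 | 1 | 1.74 | 20.9% |
| 0.7 | 2 | 1.23 | 36.8% |

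With no shift the figure is 5%. A t reference with 34 degrees of freedom lowers the ends slightly, to about 11% and 35%. At rho = 0.5, a 1-min shift gives 7.3% (k = 1) or 9.6% (k = 2).

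**The case against.** The strongest reply has four parts.

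- **The scorer is not identified.** A reader might infer that unblinded investigators score sleep onset. The protocol does not say so. Its blinding statement can be read as describing the conduct of sessions, and managing data is not the same as staging sleep. Scorer and masking rules may also sit in a document that is not shown. This stands, so silence on those details is not the finding. The finding is that Section 4.3 states a conclusion its own reason does not support.
- **CPAP state and order hardly touch the primary contrast.** This stands, as the table in the working shows. They matter mainly for the CPAP and sequence comparisons.
- **Masking cannot fully reach the contrast that matters.** This stands in part. Artefacts may reveal the simulator, and an accident-based latency cannot be masked to test type. Scoring without video, driving data or accident times still removes the most direct cues. Letting only a masked EEG score enter the analysis would go too far, because it would strip the accident criteria from the DS-MWT latency and so redefine the outcome.
- **The size is speculative.** This stands. The documents give neither a shift nor a correlation. A reader might take one striking percentage from a larger shift at a single correlation, but the documents support no such point estimate. Only a range labelled as illustrative is defensible, and it does not measure how much masking would gain.

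**Conclusion.** The concern holds in a limited form. Automatic recording is not a valid reason to expect no observer bias in an outcome that is scored afterwards, and nothing else in the protocol supplies the missing protection. For the primary contrast, the exposure is knowledge of the test type or of a simulator accident.

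The size of any bias is unknown. The 11% to 37% range shows only that a shift of 2 min, small beside the SD of 13.5 min, would not be negligible at this sample size. It rests on the assumed shift, correlation, number of pairs and independence of pairs.

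The documents do not show that biased scoring will occur, or that scoring is in fact unmasked. The point should be corrected because the protocol makes a wrong statement and the recordings needed for a partial safeguard will already exist. Sample size and session conduct are unaffected.

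**What to change.** 1. **Section 4.3:** limit the sentence to data capture. Remove the reference to sequence bias or reconcile it with O_s-1.
2. **Section 5.2, EEG scoring:** export each session's EEG, EOG and EMG under a random code, without participant number, date, visit, CPAP state or order. Whoever already does the scoring scores AASM sleep onset in random order, without video, driving or accident data. Lock the scores before the code is opened.
3. **Section 5.2, accident criteria:** keep them in the DS-MWT latency, but fix them in advance and apply them only after the EEG score is locked. Report the masked EEG-only latency alongside.

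The cost is file recoding, a locking step and a short delay before unmasking. No additional reader, patient, visit or measurement is needed. The limitation should be stated in the protocol: CPAP state and order can be withheld, but test type can be masked only partly because artefacts may reveal it.

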## 4.4 Withdrawal and discontinuation

The participants take part in the study voluntarily and confirm their consent in writing. The participants have the right to discontinue the study at any time without giving reasons. The trial management may terminate the trial participation prematurely if a participant withdraws their consent if agreements in the subject information are not adhered to or if the eligibility criteria (see 4.1) are no longer met. Trial participants whose data cannot be used in full for the analyzes due to premature termination of the trial may be replaced. The data and samples collected up to that point can still be evaluated for individual analyzes. The data will be stored in accordance with section 8.2.

If the trial participation is terminated prematurely by the trial subject or the trial management, no additional final visit is planned. In the event of premature termination at any time during that visit, the participant can leave the trial center independently. If the participant feels unwell, a person of trust can be contacted to pick them up. If no person of trust can be reached or is available, they will be driven to their home address by a taxi company.

Should an adverse event (AE) occur during or after the study, the participant can contact the sponsor-investigator or the study physician, who will then take any necessary steps. At the discretion of the sponsor- investigator or study physician, a follow-up visit may be arranged with the subject.

# STATISTICS AND METHODOLOGY

## 5.1 Statistical analysis plan and sample size calculation

There is no dedicated statistician other than the investigators involved. However, a statistician will be available throughout the study and subsequent analyzes.

See section 3.1 for primary and secondary hypotheses.

### 5.1.1 Sample size calculation

The total sample size is N_total_ = 54, consisting of the intervention group N_I_ = 36 and a healthy comparison group N_H_ = 18. (see Figure 2)

Sample sizes N_I_ = 36 for the intervention group were estimated according to formula I considering the randomized crossover RCT study design of a cohort of OSA-patients randomized both to CPAP starting condition and measurement sequence resulting in 4 groups 4 (W-DM, W-MD, C-DM, C-MD, see Figure 2) in two phases and a mixed-model ANOVA analysis. Mixed-model ANOVA accounts for the fact that repeated measures form the same person are correlated, is able to handle any missing values more effectively and considers both fixes and random effects.

[figure not shown]

Formula I

adapted from (13)

- n = Required number of participants per group.
- Z_1−α/2_​ = Z-value corresponding to the chosen significance level (e.g., 1.645 for α = 0.1 two-sided) (14).
- Z_1−β_ = Z-value corresponding to the desired power, 1.28 for 90% power) (14).
- σ = Standard deviation of the measurements = 13.5 minutes (from Bonnet & Arand) (15)
- ρ = Intra-class correlation (ICC) or correlation between repeated measures within the same participant.
- Δ = Equivalence margin or effect size = 1 pooled SD = 13.5 minutes (from Bonnet & Arand) (15)

For the sample size calculations, we use a two-sided α = 0.1 assuming that a potential difference between M and D would have a clear direction and a maximal value (bounded test range) of 40 min for the test latency. When conducting an equivalence test, using a 0.1 two-sided alpha-level effectively matches the 0.05 significance level for each side of the distribution (one for each tail), aligning the rigor of the test with the traditional hypothesis test for no difference. This assumption holds, as the reference standard deviation of 13.5 min was obtained with an equivalently bounded test range. We employ a graphically extracted and pooled standard deviation form Bonnet & Arand (15) (Figure 2 baseline and wake, p 388), the only close-to test-retest data on MWTs available.

Similarly, sample sizes N_H_ = 18 for the **comparison group** (healthy) were estimated employing a crossover without retest RCT design for the test-retest approach. We find 9 for each of two groups for 90% (assuming a two-way ANOVA), respectively (Formula II), resulting in an overall sample size of 18 for two groups. This is despite using smaller 1SD (σ) = 5.9 minutes from normative data on healthy subjects from Banks et al. (16), but is explained by the lack of additional variability-reducing conditions as compared to the OSA-cohort.

[figure not shown]

Formula II

adapted from (17)

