With these goals in mind we proposed furnishing the maintenance of wakefulness test with improved ecological validity to provide an improved tool for the assessment of the effect of excessive daytime sleepiness on the fitness to drive: we recently showed results from an exploratory feasibility study suggesting it to be well possible to transfer the MWT-paradigm to a driving simulator (DS) with high user acceptance (1). The published result’s implication and relevance was well received (2): the new test, DS-MWT, might complement somnological MWTs in pneumology and neurology. I might provide a naturalistic and relatable tool to determine EDS in traffic medicine, who is institutionally responsible for determining the FTD. This is also desirable, because prohibitively high cost - in time, money and instrumentation - often prevent a standard MWT in standard care of sleep-related medical conditions. Potentially, the use of the DS-MWT might help reduce the number of preventable road fatalities by more often identifying sleepy individuals before they get behind the wheel (2).

However, for this goal to achieve, it remains so far to be evaluated whether the latencies obtained in classical or simulation conditions are comparable and whether obtained latencies actually reflect other clinical parameters of EDS relating to underlying medical conditions, such as for example OSA. This represents a significant gap of evidence for both medical experts in pneumology and traffic medicine, but also for affected drivers. We will fill this gap by systematically comparing classical or simulation-based MWTs by means of their resulting latencies. In a within-study setup of 30 participants, we relate our experiments to a main medical comparator, a ≥7-day continuous positive airway pressure (CPAP)-withdrawal (W) and subsequent -resumption or continuation (C), respectively, in highly adherent OSA-patients (9).

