### 5.1.2 Statistical analysis plan

The primary hypothesis will be tested solely on determined mean latencies and separately from additional, secondary and exploratory analyzes. For the primary hypothesis, we will employ a mixed model ANOVA or generalized linear mixed model. All analyzes will be considered significant when p<0.05.

All secondary variables will be analyzed post-hoc for hypothesis-generation rather than formal testing. Collected secondary parameters will be analyzed *post hoc* individually with respect to the experimental condition (D/M) and the participants state (CPAP-treatment or withdrawal). If group-level differences exist we will conduct multiple comparison tests. Time-course-effects of, for example, SDLP are intended to be analyzed using repeated measures-ANOVA between 10 4-min-long modules comprising the test drive or using paired t-tests of the first and last driven module. Integrated Driving Scores (IDS, Z-scores) will be calculated after logistic regression of driving parameters.

For secondary parameter-based models, we will first use linear mixed models and stepwise testing will be based on biological/plausibility justification rather than purely statistical significance.

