## 5.3 Handling of missing data and drop-outs

Missing datasets due to participants’ withdrawal from the trial will not be multiply imputed due to the low sample size and inherently low statistical power. All available data will be used, if possible, for statistical analysis. Drop-outs during the study phase will be replaced by recruitment of new participants from the accessible participant pool, if possible.

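### Section 5.1.1 sizes the patient group per order group, although MWT and DS-MWT are compared within every patient, so the stated 90% power does not describe 36 patients (they exceed it)

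*Protocol*

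**What the plan says.** Protocol section 5.1.1 gives the size as "The total sample size is N_total_ = 54, consisting of the intervention group N_I_ = 36 and a healthy comparison group N_H_ = 18". For the patient group it describes a cohort "randomized both to CPAP starting condition and measurement sequence resulting in 4 groups 4 (W-DM, W-MD, C-DM, C-MD, see Figure 2"). The formula's result is defined as "n = Required number of participants per group". The inputs are 1.645 for significance, 1.28 for 90% power, a standard deviation of 13.5 min and a margin or effect of the same 13.5 min. The last term is "ρ = Intra-class correlation (ICC) or correlation between repeated measures within the same participant"; it is the only input without a number in the readable text. The image of Formula I is missing. On alpha the section states "For the sample size calculations, we use a two-sided α = 0.1", whereas section 5.1.2 states "All analyzes will be considered significant when p<0.05".

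Section 3.1 makes the primary comparison MWT against DS-MWT latency. Section 3.3 calls the design a within-subjects crossover, and section 4.3 places one or other test on visits 3, 4, 6 and 7. The effect of test sequence is an exploratory objective (O_s-1).

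Two other statements touch on size. The Background, and the same text in the Synopsis, says "In a within-study setup of 30 participants". Section 5.3 declines multiple imputation "due to the low sample size and inherently low statistical power".

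**The concern.** W-DM, W-MD, C-DM and C-MD differ only in when each test and each CPAP state occurs. The primary contrast is formed inside each patient and averaged over all of them, and no primary hypothesis compares the tests inside a single order group. A per-group n multiplied over order groups therefore answers a question the trial does not ask, and the power attached to it belongs to a smaller sample.

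What is at stake is the statement of what the trial can show. A reader is told that 36 patients give 90% power at 13.5 min on a 40-minute test, when the same patients can exclude a considerably smaller difference. That precision is the return on asking 36 patients to interrupt CPAP, and it is not stated. The reader also meets 30 patients in one place and low power in another, and cannot tell which account of the design is current.

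**Working it through.** **Inputs from section 5.1.1:** z = 1.645 and 1.28, σ = 13.5 min, Δ = 13.5 min, four groups, N_I = 36. **Assumed:** ρ, shown over a range, and the usual form of Formula I, n = 2(1 − ρ)(z₁ + z₂)²(σ/Δ)².

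**1. Reproducing 36.** (1.645 + 1.28)² = 8.556, doubled 17.11, and σ/Δ = 1.
- ρ = 0.5: 17.11 × 0.5 = 8.56, rounded up to 9; 9 × 4 = 36.
- n is 9 for ρ between 1 − 9/17.11 = 0.474 and 1 − 8/17.11 = 0.532.
- ρ = 0.3: 11.98, so 12, and 48 patients. ρ = 0.7: 5.13, so 6, and 24 patients.
- Another route: ρ = 0 gives 17.11, so 18 per arm, and 2 × 18 = 36.

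The 9 × 4 route is likely but inferred. The only 9 per group in print is the healthy group's, under Formula II.

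**2. Total needed for the within-patient contrast.** With one MWT/DS-MWT pair per patient, the difference has variance 2σ²(1 − ρ), so the same expression gives the total number of patients: 9 at ρ = 0.5, 12 at 0.3, 18 at 0. For 36 to be the total at exactly 90% power, ρ would have to be 1 − 36/17.11 = −1.10, which is impossible. So both routes to 36 count patients as if they were separate arms.

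**3. What 36 patients deliver.** SE = 13.5 × √(2(1 − ρ)/k)/√36, with k = 1 for one pair per patient, or k = 2 if the withdrawal and continuation pairs give independent information. TOST at one-sided 0.05, exact t with 35 df, true difference zero:

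| ρ | k | SE (min) | TOST power at 13.5 min | Margin with 90% power (min) |
|---|---|---|---|---|
| 0 | 1 | 3.18 | 98.8% | 10.7 |
| 0.3 | 1 | 2.66 | 99.9% | 8.9 |
| 0.5 | 1 | 2.25 | >99.9% | 7.5 |
| 0 | 2 | 2.25 | >99.9% | 7.5 |
| 0.3 | 2 | 1.88 | >99.9% | 6.3 |
| 0.5 | 2 | 1.59 | >99.9% | 5.3 |

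For a two-sided test of difference at 0.05 (normal approximation, k = 1), power at 13.5 min is 98.9% at ρ = 0 and above 99.9% at ρ = 0.5. The difference detectable with 90% power is 10.3 min and 7.3 min respectively.

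**4. The 30 against 36.** Thirty appears in the Background and the Synopsis background. Thirty-six appears in section 5.1.1, section 4.1 and the Synopsis entries on statistics and participant numbers. With 30 patients, TOST power at 13.5 min is still about 97% at ρ = 0 (normal approximation), so this is a conflict of figures and not a loss of adequacy.

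**The case against.** Formula I is a missing image. The 9 × 4 route cannot be confirmed, and a value of ρ may be printed in that image. This stands: the most that can be said is that no value appears in the readable text. The conclusion does not depend on the route, because step 2 applies to either.

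The order groups also have a scientific use: section 3.3 and objective O_s-1 want the influence of test sequence explored, which benefits from reasonable numbers per group. That stands as a reason for having the groups and for keeping 36. It does not make 90% the power of the primary contrast, because O_s-1 is exploratory and has no power target.

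The 90% is described as desired power, and it is met. That is true, and it limits the point. Seeing a wrong power figure next to the low-power remark in section 5.3, a reader might infer that the trial is underpowered. The documents do not support this: on their own inputs the departure is towards more power. The remark in 5.3 is offered as a reason against imputing data for withdrawals, not as a statement on the primary test. It still sits badly with a 90% target.

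A reader might also take 5.3 to 7.5 min as the margin the protocol should adopt. The documents do not support that either. Those figures rest on an assumed ρ = 0.5, and the lower one also on two independent pairs per patient. A margin reached with 90% power says what N can exclude, not what difference is clinically acceptable.

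**Conclusion.** The point holds as a misstatement of the basis and power of N_I = 36, not as a shortfall in sample size. Taking σ = 13.5 min as given and a true difference of zero for TOST, 36 patients have about 99% power at 13.5 min with ρ = 0 and more than 99.9% with ρ = 0.5. Over ρ from 0 to 0.5, the margin with 90% power is about 7.5 to 10.7 min from one pair per patient. If the pairs under withdrawal and continuation are independent, with no patient-by-test variation, it is 5.3 to 7.5 min. Missing figures mean that the design is read from the text: the DM and MD sequences and the four test visits imply one test of each kind in each CPAP state. The conflict between 30 and 36 patients, and that between low power and a 90% target, need no assumption.

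**What to change.** Keep N_I = 36 and N_H = 18, and change the wording:

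- **Section 5.1.1, patient group:** restate the calculation for the within-patient MWT versus DS-MWT contrast in all 36 patients. State the ρ used, its source and a plausible range. Report the standard error of the contrast and the difference or margin with 90% power at N = 36, under the analysis and alpha actually planned in section 5.1.2, and say whether one or two pairs per patient are counted.
- **Role of the four groups:** say that they balance order and serve the exploratory objective O_s-1, with no power claim per group.
- **Background and Synopsis background:** bring the 30 into line with N_I = 36.
- **Section 5.3:** reconcile the low-power remark with the 90% target, and give a reason for not imputing that is consistent with 5.1.1.

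The cost is a protocol text correction and a short recalculation by the sponsor. Recruitment, visits and procedures are unaffected.

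### The only stated margin, 13.5 min, is simply the SD with no tolerance argument, and the healthy sample size implies a different, unstated margin of about 5.9 min

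*Protocol*

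**What the plan says.** Section 5.1.1 sizes the OSA group with Formula I. It gives "σ = Standard deviation of the measurements = 13.5 minutes" and then "Δ = Equivalence margin or effect size = 1 pooled SD = 13.5 minutes", both from the same published source. The z-values are "e.g., 1.645 for α = 0.1 two-sided" and "1.28 for 90% power". The choice of alpha is defended on equivalence grounds: "When conducting an equivalence test, using a 0.1 two-sided alpha-level effectively matches the 0.05 significance level for each side of the distribution". A within-person correlation ρ is listed as an input, but the readable text gives no value for it. The result is 36 patients in four sequence groups, or 9 per group.

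The healthy group is said to be sized in a similar way with Formula II, giving 9 in each of two groups. The text remarks "This is despite using smaller 1SD (σ) = 5.9 minutes from normative data on healthy subjects" and continues "but is explained by the lack of additional variability-reducing conditions as compared to the OSA-cohort". It calls 5.9 min an SD and states no margin for this group. Both formulas are figures that are not available here.

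Section 3.1 makes the absence of a significant difference the primary hypothesis. Section 5.1.2 analyses it with a mixed-model ANOVA or generalized linear mixed model at p<0.05. Neither section refers to Δ.

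**The concern.** An equivalence margin should say how far two tests may differ in mean latency and still be used interchangeably. Here it is a by-product of the spread in whichever source supplied the SD. Nothing in the protocol argues that a 13.5-min difference is tolerable, and no important difference in latency is given anywhere.

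Two consequences follow. First, the same test pair would face different tolerances in the two groups if the healthy margin is what the arithmetic implies. Second, Δ is the only tolerance in the document. If the primary question is answered as the equivalence question for which alpha was chosen, 13.5 min is the number that would be used, and a wide range of true differences would pass.

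**Working it through.** **Inputs.** From section 5.1.1: σ = Δ = 13.5 min (OSA), σ = 5.9 min (healthy), z = 1.645 and 1.28, scale maximum 40 min, N = 36 and 18. Assumed: ρ = 0.5, with 0.3 to 0.7 as the range. Also assumed: c, the correlation between a patient's two D-minus-M differences (one per CPAP phase).

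**1. Reproducing 9 per OSA group.** n = 2(1.645 + 1.28)² σ²(1 − ρ)/Δ². With σ = Δ this is about 17.13(1 − ρ).
- ρ = 0.3: 11.99, so 12 per group (48 in total)
- ρ = 0.5: 8.56, so 9 per group (36 in total)
- ρ = 0.7: 5.14, so 6 per group (24 in total)

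The stated 36 is recovered for ρ from about 0.475 to 0.532. The SD plays no part, but ρ does.

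**2. Reproducing 9 per healthy group.** n = (1.645 + 1.28)²(σ/Δ)² = 8.56(5.9/Δ)².
- Δ = 5.9: 8.56, so 9
- Δ = 13.5: 1.64, so 2

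Solving for n = 9 gives Δ between about 5.8 and 6.1 min. With the unpaired form without ρ, n = 17.13(5.9/Δ)², 9 per group would need Δ between 5.9√(17.13/9) = 8.1 and 5.9√(17.13/8) = 8.6, and Δ = 13.5 would give 4. On neither form is the healthy margin 13.5 min. The form that also yields the OSA figure points to one SD.

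**3. Scale.** 13.5/40 = 34%. 5.9/40 = 15%. 13.5/5.9 = 2.3.

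**4. What a 13.5-min margin would accept in 36 OSA patients.** SD of the difference = 13.5√(2(1 − 0.5)) = 13.5 min.
- One phase: SE = 13.5/6 = 2.25
- Two phases with c = 0.5: SE = 2.25√(1.5/2) = 1.95

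The chance of declaring equivalence at true gap δ is about Φ((13.5 − δ)/SE − 1.69). Simulated with two one-sided t-tests:

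| True gap | One phase | Two phases, c = 0.5 |
|---|---|---|
| 7 min | 88% | 95% |
| 8 min | 77% | 87% |
| 10 min | 45% | 55% |

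On one phase the 90% CI half-width is 3.8 min, so an observed difference up to 9.7 min passes. A difference from about 4.6 min is significant at p<0.05. An observed result between those values would be both significantly different and equivalent.

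**5. Healthy group at the implied 5.9 min.** SE = 5.9/√18 = 1.39. A true 7-min gap passes in 0.8% of trials at ρ = 0.5.

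**6. What N = 36 supports.** Power at a true difference of zero is about 2Φ(m/SE − 1.69) − 1. The cells show one phase / two phases with c = 0.5 / two phases with c = 0, from simulation:

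| ρ | Margin 7.5 min | Margin 5.9 min |
|---|---|---|
| 0.3 | 74 / 88 / 98% | 40 / 61 / 85% |
| 0.5 | 90 / 97 / >99% | 64 / 81 / 95% |

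**The case against.** The strongest reply is that the margin decides nothing. Δ appears only in the sample-size section, is labelled as either a margin or an effect size, and the planned analysis is a difference test. That stands. A reader might infer that this trial will declare materially different tests equivalent, but the protocol contains no rule that would do so. It also offers no anchor for what counts as materially different. The percentages above describe what would happen if the stated Δ were adopted as the decision limit.

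Three further limits stand:
- The healthy margin is not stated. Formula II is not available, so 5.9 min is an inference, and the verdict on the healthy-group explanation depends on it.
- It would be too strong to say that 9 per group follows regardless of inputs. Only the SD cancels, and ρ still drives the OSA figure.
- 5.9 min is itself a source SD, and 7.5 min is what the planned N happens to support. Neither is a clinical tolerance.

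It can also be said that a standardised effect legitimately gives different minutes in groups with different spread. That is reasonable for an effect size but not for a tolerance on interchangeability, and section 5.1.1 justifies its alpha by equivalence testing. If Δ is instead read as an effect size, the group is sized to detect a one-SD difference. That is a weak basis for concluding that the tests do not differ.

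Finally, the protocol's own per-group formula at 5.9 min gives 8.56(13.5/5.9)² = 44.8, or 45 per group and 180 in total. The D versus M comparison, however, is made within all 36 patients, so that figure is not the cost of a tighter margin.

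**Conclusion.** The point holds in a conditional form. Stated in the protocol: Δ equals σ at 13.5 min, 34% of the scale, with no tolerance argument. Inferred: a healthy margin of about 5.9 min, 2.3-fold smaller. On that reconstruction the remark that the smaller SD fails to reduce the healthy sample size for want of variability-reducing conditions does not follow, because the margin shrank with the SD.

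If equivalence were judged at 13.5 min, true gaps of 7 to 10 min would pass in roughly 45% to 95% of trials in OSA patients, while a 7-min gap would almost never pass in healthy participants. These figures rest on ρ = 0.5 and on one phase or two phases correlated at 0.5. At ρ = 0.3 on one phase the OSA figures for 7, 8 and 10 min are 77%, 65% and 36%. The margin needs a justification and a place in the analysis before it can support any conclusion of equivalence.

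**What to change.** 1. In section 5.1.1, state one margin in minutes, common to both groups, and justify it as a tolerable difference in mean latency rather than as the SD of a source.
2. In section 5.1.2, state that the 90% CI for the D minus M difference is compared with that margin.
3. State the value of ρ and how the two phases are combined, and restate the power of the existing 36 patients for the within-patient comparison at the chosen margin. The table in step 6 of the working shows the range: at ρ = 0.5, about 90% (one phase) to 97% (two phases, c = 0.5) at 7.5 min, and 64-95% at 5.9 min. At ρ = 0.3 the ranges are 74-98% and 40-85%.
4. State the healthy Δ. If it is 5.9 min, replace the explanation of the healthy sample size by saying that 9 per group results from setting the margin equal to the SD.

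The cost is protocol wording and possibly a less favourable stated power. No extra patients or procedures are needed to make the change.
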